#### 2.1.7 Randomization.

Sampling in the quantitative phase will be conducted in two stages. In the first stage, a list of all hospitals in the province (26 hospitals) will be prepared through Mazandaran University of Medical Sciences, from which 10 hospitals will be randomly selected. The names of the hospitals will be written on cards, placed in a box, mixed, and then 10 cards will be drawn one by one. In the second stage, participants will be selected from each hospital using random sampling based on the number of nurses employed in each facility. Each hospital will provide a list of nurses’ IDs to the study coordinator, who will code these identifiers and create a master list. The required number of samples will then be selected from this list using a random number table, after which the selected individuals will be contacted to assess their eligibility and willingness to participate.

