**Methods:**

Utilizing a mixed-method protocol, the research consists of two distinct phases. The quantitative phase employs a two-stage sampling method to select participants from ten randomly chosen hospitals within a province, ensuring a representative sample. In the qualitative phase, snowball sampling will be utilized to achieve data saturation, allowing for a comprehensive understanding of the factors influencing happiness in nursing. Data collection will involve a range of instruments, including a demographic characteristics and occupational features checklist, the Oxford Happiness Questionnaire, and semi-structured interviews to gather in-depth insights. Data analysis will be conducted using SPSS-24 statistical software for quantitative data and MAXQDA for qualitative data, enabling a robust examination of the findings.

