#### 2.1.5 Data collection.

Data will be collected using the following instruments:

A. self-design checklist including demographic characteristics and occupational features.B. The standard Oxford Happiness Questionnaire, which will be sent to participants online.

**A. Checklist of demographic characteristics and occupational features:** This checklist will include demographic characteristics and occupational features.

The demographic section will cover: Age, Gender, Number of children, Marital status, Educational background, Spouse’s employment status, Type of housing, Family income, Engagement in recreational or cultural activities, Satisfaction with physical health, Satisfaction with mental health.

The occupational features section will include: Official position of nurses, Employment status, Current department of the workplace, Level of interest in nursing at present, Satisfaction with salary, Number of overtime hours, Shift work, Engagement in recreational activities at the workplace.

**B. Oxford Happiness Questionnaire:** The Oxford Happiness Questionnaire consists of 29 items divided into six subscales: self-esteem, life satisfaction, efficiency, positive mood, sense of control, and mental health. Respondents will answer items on a six-point Likert scale ranging from “strongly disagree” to “strongly agree.” The scoring for the six scales ranges from 1 to 6, leading to a total score that ranges from 29 to 174. A higher score indicates greater happiness. The total score will be classified into three levels: less than 100 indicates low happiness, scores between 101–131 indicate medium happiness, and scores above 132 indicate high happiness [24,25]. The validity and reliability of the Persian version of the questionnaire have been confirmed in previous studies, with a reported Cronbach’s alpha of over 0.90 [24–26].

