#### 2.1.6 Sample size.

The initial sample size was calculated using the formula for estimating a population mean: n=(Zα/2 × σ/d)2n=(Zα/2 × σ/d)2. Based on a previous similar study [27], the mean happiness score was 67.43 with a standard deviation (SD) of 17.28. Assuming a 95% confidence level (Zα/2 = 1.96Zα/2 = 1.96) and a margin of error (d) of 2 points, the calculated sample size was 287. However, to account for the two‑stage cluster sampling design where hospitals are first randomly selected, followed by the random selection of nurses within each hospital proportionate to the hospital’s nursing staff size a design effect (DE) will be incorporated into the sample size calculation. The design effect is computed using the formula DE = 1 + (m − 1) × ICC, where m represents the average cluster size (the number of participants per hospital) and ICC denotes the intra‑cluster correlation coefficient. Based on previous similar studies conducted in Iran examining health outcomes among healthcare workers, an ICC of 0.05 is assumed for happiness‑related variables among nurses within the same hospital. With an estimated average cluster size of 34 nurses per hospital (derived by dividing the total target sample by the number of hospitals), the design effect is calculated as 1 + (34 − 1) × 0.05 = 2.65.

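### Drawing 10 of 26 hospitals from one unstratified box is valid but inefficient for the overall mean: at the protocol's own SD and ICC, ±2 points is out of reach with ten hospitals at any realistic number of nurses

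*Protocol article*

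**What the plan says.** Section 2.1.7 has a list of 26 hospitals, "from which 10 hospitals will be randomly selected" by drawing cards from a single box. No stratification by size or type is described. Within each drawn hospital, nurses are sampled at random in proportion to staff, from an ID list that the hospital supplies. Section 2.1.5 gives the mode: "The standard Oxford Happiness Questionnaire, which will be sent to participants online". Section 2.1.2 defines the target as nurses in hospitals affiliated with the one university, which is a finite set. The abstract describes the sample as "participants from ten randomly chosen hospitals within a province, ensuring a representative sample".

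Section 2.1.6 sets the precision. It takes from a previous study that "the mean happiness score was 67.43 with a standard deviation (SD) of 17.28", uses 95% confidence "and a margin of error (d) of 2 points, the calculated sample size was 287", and calls this size initial. It adds that "an ICC of 0.05 is assumed for happiness‑related variables among nurses within the same hospital". Taking 34 as the mean number sampled at each site, it arrives at a design effect of 2.65. No final total is given. No reason is given for stopping at ten hospitals.

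**The concern.** Sampling a subset of hospitals leaves an error component that depends only on which hospitals are drawn. More nurses in the same ten hospitals cannot reduce it. Restricting the number of sites is usually justified by the cost of working at each one. Here the frame is already listed and the main instrument is sent online, so the trade-off deserves an explicit look.

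At stake is the precision of the descriptive result: the mean happiness score and, by extension, the prevalence of each happiness level. If the hospital component alone is about as large as the target margin, completing the design-effect step in section 2.1.6 cannot rescue the target.

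**Working it through.** **Inputs.** SD 17.28, z = 1.96, margin 2, ICC 0.05 and 34 nurses per hospital (section 2.1.6); 10 of 26 hospitals (section 2.1.7).

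**The plan's own figures.**
- (1.96 × 17.28 / 2)² = 286.8, so 287 reproduces.
- 1 + (34 − 1) × 0.05 = 2.65 reproduces.
- 34 × 10 = 340 nurses, whereas 287 × 2.65 = 761. Both totals are carried below because the final one is not stated.

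**Variance of the mean**, with k hospitals and n nurses:
- Between hospitals: 0.05 × 17.28² / k = 14.93 / k. It is multiplied by (1 − k/26) if the 26 hospitals are the whole population.
- Within hospitals: 0.95 × 17.28² / n = 283.67 / n.
- Margin = 1.96 × √(sum). Without the finite factor this is the protocol's design-effect formula.

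**Floor with ten hospitals** (between-hospital part only):
- No finite factor: 1.96 × √1.493 = ±2.39. No number of nurses reaches ±2.
- With 1 − 10/26 = 0.615: 1.96 × √0.919 = ±1.88. Reaching ±2 then takes about 2,316 nurses.

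**Margins at ICC 0.05:**

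| Nurses | 10 hospitals, no finite factor | 10 hospitals, with factor | 26 as a sample | 26 as strata |
|---|---|---|---|---|
| 287 | ±3.09 | ±2.71 | ±2.45 | ±1.95 |
| 340 | ±2.99 | ±2.60 | ±2.33 | ±1.79 |
| 761 | ±2.68 | ±2.23 | ±1.91 | ±1.20 |

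Example: 287 nurses, ten hospitals, with factor: 1.96 × √(0.919 + 283.67/287) = 1.96 × √1.907 = 2.71. With all 26 as strata the first term is zero: 1.96 × √(283.67/287) = 1.95.

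**Nurses needed for ±2 with 26 hospitals.** The variance must not exceed (2/1.96)² = 1.041. As strata: 283.67 / 1.041, so 273. As a sample of hospitals: 283.67 / (1.041 − 0.574), so 608.

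**Simulation** (20,000 runs, 26 hospitals as the whole population). For 287 nurses in all 26, the margin is ±1.95 with equal hospital sizes and ±1.96 with unequal sizes (assumed coefficient of variation 0.7). For 340 nurses in ten hospitals it is ±2.59 and ±2.87.

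**Sensitivity to the ICC** (287 nurses, 26 as the whole population; ten hospitals versus all 26):
- 0.01: ±2.16 versus ±1.99
- 0.02: ±2.31 versus ±1.98
- 0.10: ±3.26 versus ±1.90

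At ICC 0.01, 340 nurses in ten hospitals already give ±2.01.

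**Sensitivity to the SD** (assumed values; 287 nurses, 26 strata): SD 20 gives ±2.26 and SD 25 gives ±2.82.

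**The case against.** The strongest reply is that nothing here is an error. A simple random draw of hospitals followed by proportional sampling of nurses is a probability sample. The plan also recognises clustering, through a design effect, a random intercept, an ICC and Rao-Scott tests. That stands. A reader might infer that an unstratified draw contradicts the claim of representativeness. It does not: a draw that happens to miss a kind of hospital adds variance, not selection bias. The chance of missing a given type cannot be calculated from the documents, which give no counts by type.

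A reader might also infer that using all 26 hospitals simply makes 287 nurses and ±2 attainable. The documents do not support that without conditions. Section 2.1.8 treats hospital as a random intercept. Carried over to the overall mean, that gives ±2.45, and ±2 needs 608 nurses. Eligibility and willingness are checked only after selection, and 287 leaves room to lose just 14 responses. The SD comes with a mean of 67.43, well inside the low band of the 29–174 score, so its fit to that score is uncertain. Nor should ±3.09 be set against ±1.95, because the two figures refer to different target populations.

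Saying that ten hospitals save little would also go too far. Written consent is required before the survey, selected nurses are contacted individually, and section 5.1 cites limited time and resources. The documents give no cost figure.

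Finally, part of the shortfall at 287 or 340 comes from the unfinished design-effect step. But even the fully inflated 761 leaves ±2.23 with the finite factor, so the number of hospitals remains the binding limit at ICC 0.05.

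**Conclusion.** The point holds as one of efficiency, not validity. With SD 17.28 and ICC 0.05, ten hospitals cannot deliver ±2 by the protocol's own formula (floor ±2.39), and cannot do so realistically even with the finite correction (floor ±1.88, about 2,316 nurses).

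Like for like at 287 completed responses, using all 26 hospitals cuts the margin from ±2.71 to ±1.95 (a finite population of 26) or from ±3.09 to ±2.45 (hospitals as a sample). The target is met at that size only on the first reading, and only if at least 273 responses are complete and the SD holds. With an ICC near 0.01 the gain is negligible.

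The benefit concerns the overall mean and prevalence (no prevalence margin was computed). It matters much less for the nurse-level associations in the five hypotheses of section 2.1. All figures assume that the 26 hospitals are the target frame. Section 2.1.7 speaks of hospitals in the province and section 2.1.2 of affiliated hospitals, so this should be confirmed.

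**What to change.** Recruitment has not begun, so either change is still open.

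1. **Minimum.** Sort the 26 hospitals by nursing staff size, and by type if known, and draw the ten from these strata in proportion. This is nearly free. It reduces hospital-sampling error but does not remove it, so the achievable margin should be restated.
2. **Preferred.** Include every hospital in the target frame and allocate the same total of nurses in proportion to staff. With 26 hospitals, 287 nurses average about 11 per hospital and 340 about 13. State that hospital is a stratum for the descriptive mean and prevalence; the random intercept can remain for the association models. State the number of completed responses required, and recruit above it.

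The preferred change needs no more nurses. It costs up to sixteen more ID lists and site permissions, and consent contacts at those extra sites. Interviews can stay in a subset of hospitals. If ten hospitals are kept for practical reasons, give the reason and replace the ±2 target with the margin that ten hospitals can support.

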#### 2.1.8 Statistical analysis.

In the first phase of the study, data will be analyzed using SPSS-24 and STATA/MP software. To account for the two-stage sampling design and potential clustering effects (nurses nested within hospitals), linear mixed-effects models will be employed with ‘hospital’ included as a random intercept. This approach will provide robust standard errors and correct estimates of variance. The intra-class correlation coefficient (ICC) will be calculated to assess the degree of clustering. For categorical variables, Rao-Scott chi-square tests will be used. A significance level of 0.05 will be maintained for all tests. The extent and pattern of missing data will be assessed using Little’s MCAR test. Data are assumed to be Missing at Random (MAR). Instead of mean imputation, Multiple Imputation by Chained Equations (MICE) will be used to handle missing values in both demographic and outcome variables, generating 20 imputed datasets. The results from these datasets will be pooled using Rubin’s rules. A sensitivity analysis will be conducted by comparing results from the complete-case analysis with those from the multiple imputation approach to ensure robustness.

The first phase of this study, a cross-sectional survey of happiness among nurses in hospitals affiliated with Mazandaran University of Medical Sciences, aims to provide a comprehensive understanding of the factors influencing nurses’ well-being. By employing standardized instruments, including the Oxford Happiness Questionnaire, this phase will quantify happiness levels and identify key demographic and occupational variables that contribute to or detract from happiness in the workplace. The findings are expected to highlight critical areas for intervention, which could lead to improved job satisfaction and overall well-being among nurses. Ultimately, this phase will lay the groundwork for subsequent qualitative research, facilitating a deeper exploration of the lived experiences of nurses and informing targeted strategies to enhance their happiness in the profession.

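### The complete-case versus multiple-imputation comparison leaves the missing-at-random assumption untested, so agreement between the two does not show robustness to its failure

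*Protocol article*

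**What the plan says.** Section 2.1.8 (Statistical analysis) of the protocol article sets out the handling of missing data in four steps.

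- **Diagnostic:** "The extent and pattern of missing data will be assessed using Little’s MCAR test".
- **Assumption:** missing at random (MAR).
- **Method:** multiple imputation by chained equations, which "will be used to handle missing values in both demographic and outcome variables, generating 20 imputed datasets", pooled by Rubin's rules.
- **Sensitivity analysis:** "comparing results from the complete-case analysis with those from the multiple imputation approach to ensure robustness".

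Nothing else in the article departs from MAR.

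Three other places bear on the point. Under section 2.1.5 the Oxford Happiness Questionnaire is the outcome, "which will be sent to participants online", and the accompanying checklist includes satisfaction with physical and mental health, interest in nursing and satisfaction with salary. Section 2.1.4 excludes nurses who are unwilling to cooperate during the survey. Section 2.1.7 has willingness assessed when selected nurses are contacted. Section 2.1.6 sizes the survey for a mean score with a margin of 2 points.

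**The concern.** A sensitivity analysis should relax the assumption on which the main analysis rests. Here that assumption is that, given what was observed, missingness does not depend on the unobserved happiness score. Complete-case analysis does not relax it. For a mean it needs the stricter condition that data are missing completely at random (MCAR). For a regression of happiness on covariates it needs missingness not to depend on the outcome given those covariates. Little's test does not fill the gap, because it addresses MCAR and cannot separate MAR from score-dependent missingness.

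If unhappier nurses tend to leave the happiness items unfinished for reasons the checklist does not capture, both analyses overstate the mean. They may also sit close together. A reader following the stated purpose of the comparison could then report the result as robust when the key assumption had not been examined. At stake are the happiness level and its categories, which are the main descriptive output of phase 1, and the associations in the section 2.1 hypotheses.

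**Working it through.** **Planning figures reproduced.** Section 2.1.6 states that "the mean happiness score was 67.43 with a standard deviation (SD) of 17.28", and gives a "margin of error (d) of 2 points, the calculated sample size was 287". The formula gives (1.96 × 17.28 / 2)² = 286.8, which rounds up to 287 and matches. The design effect 1 + 33 × 0.05 = 2.65 also reproduces. No stated figure is disputed. These values only set the scale.

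**Analytic size.** Bias in the imputed mean = fraction of scores missing × (mean predicted under MAR − true mean of the missing nurses). The article gives neither input, so both are assumed.

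| Missing | 5 points below MAR prediction | 10 points below |
|---|---|---|
| 5% | 0.05 × 5 = 0.25 | 0.05 × 10 = 0.5 |
| 10% | 0.10 × 5 = 0.5 | 0.10 × 10 = 1.0 |
| 20% | 0.20 × 5 = 1.0 | 0.20 × 10 = 2.0 |

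**Would the planned comparison show it?** A simulation used the protocol's mean of 67.43, SD of 17.28, ICC of 0.05 and 10 hospitals of 34 nurses (340). It had 20 imputations and 1,000 replicates, with hospital and one predictor in the imputation model. Assumed inputs were a predictor correlation of 0.3 with happiness and a logit slope for missingness of −1, either on the predictor (MAR) or per SD of the happiness score (not MAR). Bias in the mean, in points:

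| Mechanism | Missing | Complete case | Imputation | Gap |
|---|---|---|---|---|
| MAR | 10% | +0.46 | −0.01 | 0.46 |
| MAR | 20% | +0.90 | +0.01 | 0.88 |
| MAR | 30% | +1.32 | 0.00 | 1.31 |
| Score-dependent | 10% | +1.57 | +1.37 | 0.19 |
| Score-dependent | 20% | +2.95 | +2.59 | 0.36 |
| Score-dependent | 30% | +4.38 | +3.86 | 0.52 |

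With MCAR data both biases were about zero. In this set-up the two methods lie closer together when MAR fails than when it holds and imputation is unbiased. The size of the gap therefore does not indicate whether MAR holds.

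The slope on the predictor (true value 0.3 × 17.28 = 5.18) behaves similarly under score-dependent missingness. At 10%, 20% and 30% missing it is attenuated by 0.31, 0.52 and 0.71 in complete cases and by 0.29, 0.50 and 0.68 after imputation. The two methods differ by less than 0.03.

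The simulated mechanism is stronger than the analytic range above. At 20% missing, an imputation bias of 2.59 implies 2.59 / 0.20 ≈ 13 points of unexplained difference. The simulation shows how the comparison behaves and does not forecast this survey's bias.

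**Dependence on the predictors.** A simplified single-level, large-sample version with 20% score-dependent missingness gives:

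| Correlation of predictors with happiness (assumed) | Complete case | Imputation | Gap |
|---|---|---|---|
| 0.3 | 3.0 | 2.8 | 0.2 |
| 0.7 | 3.0 | 1.6 | 1.4 |

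With strong predictors the methods diverge visibly and imputation removes nearly half the bias. Even then 1.6 points remain, and the comparison gives no measure of that remainder.

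**The case against.** The strongest reply is that this is a condensed article, that a statistical analysis plan may add further analyses, and that an analysis under non-random missingness is typical content for such a plan. That stands as far as absence goes: a reader might infer that the study will have no such analysis, and the article cannot show this. What remains is that the article names a specific comparison and gives it a purpose it cannot serve with respect to MAR.

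It is also fair to say that the purpose is loosely worded and can be read as checking whether imputation changes the answer. The comparison does that, and it has value for showing departure from MCAR. The article nowhere says that agreement will be taken as proof of MAR.

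Three stronger readings are tempting and are not supported:

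- **That non-completion by unhappy nurses is the most likely mechanism.** The article states no missing-data rate or mechanism. Its limitations (section 5.1) mention self-report response bias and sampling bias, not missing scores. The mechanism is plausible, no more.
- **That the two analyses will agree, so the check passes exactly when MAR fails.** Agreement depends on how well the checklist predicts happiness. Several items in section 2.1.5, such as satisfaction with mental health, may predict it well, and a partly completed questionnaire also carries information.
- **That the bias uses up the whole planned margin.** Two points is the extreme corner of the assumed range. The 5–10 points must also be the difference left after imputation. If covariates explained half of a raw difference of that size, 0.5–2.0 would become 0.25–1.0. Moreover, the 2-point margin is the simple-random-sampling figure. With 340 nurses and the design effect, the half-width is 1.96 × 17.28 × √(2.65/340) = 2.99.

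**Conclusion.** The concern holds in a limited form. Because neither analysis allows missingness to depend on the unseen score, their agreement cannot establish robustness to departures from MAR, and their disagreement does not establish such a departure. The possible error in the mean is about 0.5–2.0 points, assuming 10–20% of scores missing and those nurses 5–10 points below the MAR prediction. It is 0.25–0.5 points at 5% missing. Associations can be attenuated without the comparison showing it. The logical point does not depend on these assumptions; its practical weight does, and it could be small if few scores are missing or the checklist explains most of the difference. It is a worthwhile improvement and does not invalidate the planned analysis.

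**What to change.** Pre-specify a delta-adjusted analysis on the 20 planned datasets: lower the imputed happiness scores by fixed amounts, for example 2, 5 and 10 points (about 0.12, 0.29 and 0.58 of the planning SD: 2/17.28, 5/17.28, 10/17.28). At each shift report the mean, the three happiness categories and the hypothesis results, pooled by Rubin's rules as already planned. Keep the complete-case comparison, but reword section 2.1.8 so that it is said to show only the effect of imputing under MAR.

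The cost is a few extra lines of analysis. The article states that recruitment had not begun, so the shifts can be fixed before data are seen. There are two downsides. The shift sizes are a judgement that must be made and justified in advance. The analysis also covers only nurses in the imputed data: those who refuse at contact (section 2.1.7) or are excluded for non-cooperation (section 2.1.4) are a separate selection problem that it does not address.

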**Conclusions:**

The anticipated outcomes of this study highlight the positive impact of workplace happiness on nurses’ health, job satisfaction, and overall quality of patient care. By identifying actionable perceived strategies to promote happiness in the workplace, this research aims to contribute to the development of supportive environments that enhance both staff well-being and patient outcomes. Ultimately, this study represents a vital step toward fostering a healthier, more engaged nursing workforce.

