## 2. Materials and methods

This protocol describes a mixed-methods investigation approved by the Ethics Committee for Health Research Ethics of Mazandaran University of Medical Sciences (approval code: IR.MAZUMS.IMAMHOSPITAL.REC.1402.119). The study consists of two phases. The first phase involves a cross-sectional survey, and the second phase comprises semi-structured interviews. All procedures will be conducted in accordance with the ethical principles outlined in the Declaration of Helsinki and relevant national guidelines. Written informed consent will be obtained from all participants prior to their involvement in any study-related procedures, including both the quantitative survey and qualitative interviews. An overview of the different phases containing aims, methods, and participants are depicted in Table 1.

**Table 1 pone.0354376.t001:** The study overview.

Phases	Aim	Methods	Participants

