### 2.1 Study 1: Cross‑sectional survey

This study adopts a sequential explanatory mixed‑methods design. The rationale for this design is that the quantitative phase (cross‑sectional survey) will first identify the levels and correlates of happiness among nurses. Subsequently, the qualitative phase (semi‑structured interviews) will be used to explain, elaborate on, and provide contextual depth to the quantitative findings. This design is well‑suited to our aim of developing evidence‑based, actionable strategies, as the qualitative data will help interpret statistical patterns and uncover the mechanisms underlying the observed relationships. The primary aim of the first phase of this study is to conduct a cross-sectional investigation into the levels of happiness among nurses working in hospitals. This quantitative approach will involve the administration of standardized surveys to assess various dimensions of happiness, including emotional, social, and cognitive components. By collecting data from a diverse sample of nurses across different hospital settings, the study seeks to quantify happiness levels and identify factors that contribute to or hinder happiness in the workplace. The findings will provide a comprehensive overview of the current state of happiness among nurses, highlighting areas that require attention and intervention. To achieve this aim, the following research hypotheses will be tested:

There is a significant relationship between demographic variables (age, gender, marital status, family income) and nurses’ happiness scores.There is a significant relationship between occupational variables (work experience, employment status, salary satisfaction, overtime hours, shift work) and happiness scores.Nurses who participate in recreational and cultural activities (either at the workplace or outside of it) have higher happiness scores compared to nurses who do not participate in such activities.Satisfaction with physical and mental health has a significant positive correlation with nurses’ happiness scores.A regression model encompassing demographic and occupational variables will be able to significantly predict a portion of the variance in nurses’ happiness scores.

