## 4. Result

The anticipated results of this study include a detailed understanding of the current state of happiness among nurses and the identification of factors that significantly influence their well-being. Quantitative data, collected through validated instruments such as the Oxford Happiness Questionnaire, are expected to reveal patterns and correlations between happiness levels and various demographic and occupational characteristics, including age, years of experience, job roles, and shift patterns. These findings aim to provide a statistical foundation for understanding the prevalence and distribution of happiness in the nursing profession.

In the qualitative phase, semi-structured interviews are anticipated to yield rich, contextual data, uncovering deeper insights into the lived experiences of nurses. Thematic analysis is expected to highlight critical themes, such as the role of workplace culture, management support, peer relationships, opportunities for professional growth, and the impact of work-life balance on happiness.

By synthesizing the quantitative and qualitative findings, the study aims to construct a holistic framework for understanding happiness in nursing. This comprehensive approach is expected to inform actionable strategies tailored to address both systemic and individual factors that impact happiness. These strategies will contribute to fostering a positive work environment, ultimately enhancing nurse retention, reducing burnout, and improving patient care outcomes.

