#### Limitations include.

Sampling Bias: There might be limitations in the generalizability of the results if the sample is not representative of the broader population of nurses.Self-Report Measures: Reliance on self-report measures for assessing happiness may introduce response bias and lack of objectivity.Time and Resource Constraints: Conducting a mixed-methods study can be resource-intensive and time-consuming, which may limit the scope and depth of the research.

Overall, we will try to address these weaknesses through careful sampling strategies, methodological rigor, and adequate resource allocation can enhance the quality and validity of the research on investigating happiness in nurses.

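### A one-time self-report survey can show what is associated with nurses' happiness, but the stated aims and the abstract announce what contributes to it and what it improves

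*Protocol article*

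**What the plan says.** The Protocol article, section 2, sets out the design: "The first phase involves a cross-sectional survey, and the second phase comprises semi-structured interviews". Section 2.1.5 lists the Phase 1 instruments, a checklist of demographic and occupational features and the Oxford Happiness Questionnaire, with no repeat administration.

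The purpose of Phase 1 is worded directionally in three places. Section 2.1.8 says the survey will "identify key demographic and occupational variables that contribute to or detract from happiness in the workplace". Section 2.1 says it will "quantify happiness levels and identify factors that contribute to or hinder happiness in the workplace". The aim column of Table 1 is phrased in the same way.

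The abstract's Conclusions add an effect running the other way, from happiness to other outcomes: "The anticipated outcomes of this study highlight the positive impact of workplace happiness on nurses’ health, job satisfaction, and overall quality of patient care".

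Section 4 expects strategies built on the combined findings to improve the work environment, "ultimately enhancing nurse retention, reducing burnout, and improving patient care outcomes".

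The limitations in section 5.1 cover representativeness of the sample, self-report and resources. The self-report item reads: "Reliance on self-report measures for assessing happiness may introduce response bias and lack of objectivity".

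**The concern.** When happiness and its correlates are recorded at one moment, an association fits at least three explanations: the factor raises happiness, happier nurses report more of the factor, or something else drives both. If happiness scores are higher among nurses who take part in recreation, for example, the survey cannot tell whether recreation helps or whether happier nurses join in.

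The wording matters because of where the results go. Section 2.1.8 expects the survey to point to areas for intervention. Section 2.2.5 uses the survey results to refine the interview guide. Section 2.2.7 says the integrated interpretation will feed the recommended strategies. Section 1.2 addresses those recommendations to administrators and policymakers as evidence-based. An association described as a contribution can pass along this chain without anyone marking that its direction was never established.

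The sentence in the abstract raises a second problem. It announces an impact on outcomes for which the study has no measure, or only nurses' perceptions.

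**Working it through.** No arithmetic decides this point. The check sets the stated claims beside what is measured and when.

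**1. Time order.** Checklist and questionnaire belong to one cross-sectional survey, so no correlate is recorded before the happiness score. Some correlates are nonetheless fixed by their nature (age, gender). Others are current attitudes or behaviours.

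**2. How many correlates are affected.** Section 2.1.5 lists 11 demographic and 8 occupational items, 11 + 8 = 19. Six are concurrent attitudes or behaviours for which either direction is plausible:
- interest in nursing at present
- satisfaction with salary
- satisfaction with physical health
- satisfaction with mental health
- recreational or cultural activity
- recreational activity at the workplace

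That is 6/19, about a third. At least one of them is named in three of the five hypotheses in section 2.1: the second (salary satisfaction), the third (recreation) and the fourth (health satisfaction).

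**3. Overlap in content.** Section 2.1.5 states: "The Oxford Happiness Questionnaire consists of 29 items divided into six subscales". One of those subscales is mental health. Satisfaction with mental health is therefore a correlate of a total score that already contains a mental-health part, and some of that correlation may be shared content.

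**4. The announced impact against the measures.**

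| Outcome in the abstract's Conclusions | Phase 1 (section 2.1.5) | Phase 2 (section 2.2) |
|---|---|---|
| Nurses' health | Two self-rated satisfaction items; one questionnaire subscale | Mental health appears as an influence on happiness, the opposite direction |
| Job satisfaction | No overall measure; nearest items are salary satisfaction and interest in nursing | Not named in the question on impact |
| Quality of patient care | No measure | Nurses' perceived impact |

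The Phase 2 question on impact asks for nurses' views on performance, patient care and interactions with colleagues. It yields perceptions, which do not demonstrate an effect.

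**5. Whether the analysis or sample size could repair it.** Section 2.1.8 plans a random intercept for hospital and multiple imputation. These deal with clustering and missing data, not direction. The initial sample size in section 2.1.6 reproduces: (1.96 × 17.28 / 2)² = 286.8, rounded up to 287. It governs the precision of a mean, and no larger number would supply time order or an unmeasured outcome.

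**6. The limitations.** The self-report item concerns how accurately happiness is measured. None of the three limitations mentions time order, reverse causation or confounding.

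**The case against.** The strongest reply is that the part of the plan that will be tested is already worded correctly. The five hypotheses in section 2.1 speak of relationships, a difference between groups, a correlation and prediction of variance. The abstract's Result paragraph promises correlation. Identifying strategies is assigned to Phase 2, and the article repeatedly calls them perceived strategies. The joint display in section 2.2.7 is meant to show where interviews contradict the statistics as well as where they confirm them. No planned estimate or test would change.

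Most of this stands. It places the fault in the stated aims, the abstract and the limitations, not in the hypotheses or the models. It does not remove the fault, because the article then tests associations and announces contributions and impact.

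Four stronger readings are tempting, and the documents do not support them.
- A reader might infer that the study will report an impact of happiness on burnout and retention. The abstract's sentence names neither. They appear in section 4 as hoped-for effects of later strategies.
- A reader might infer that a statement about patient care would have no data behind it. Phase 2 does collect perceived impact on care.
- A reader might infer that health is only a self-rated correlate. Mental health is also part of the outcome questionnaire.
- A reader might infer that survey coefficients become recommendations directly. The article routes them through the interviews and the integration step.

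**Conclusion.** The point holds as a mismatch between design and stated inference. Phase 1 can report associations. It cannot establish which variables contribute to, detract from or hinder happiness, and for six of the 19 checklist items either direction is plausible. Of the three outcomes in the abstract's sentence, two (overall job satisfaction and quality of care) have no measure in Phase 1, and the third (health) has only self-rated items and a subscale. At most the study can report how nurses perceive the impact on performance, care and relations with colleagues.

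This should be corrected because it changes what the study may conclude and recommend, although the planned analysis survives intact.

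The verdict assumes that the instrument list in section 2.1.5 is complete. If the full checklist contains an overall job-satisfaction measure, that part of the second point falls to an association at one time. The absence of time order would remain.

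**What to change.** - In Table 1, the aim in section 2.1 and section 2.1.8, replace the directional wording with *associated with*. Leave the hypotheses as they are.
- Recast the abstract's Conclusions as nurses' perceived impact of happiness, drawn from Phase 2 and limited to what its question covers.
- In section 4, present the benefits for retention, burnout and patient care as untested rationale for later strategies.
- Report correlates fixed before the current state of happiness, such as age and gender, separately from concurrent attitudes and behaviours. In the joint display, label strategies that rest only on the second group as hypothesis-generating.
- Add lack of time order and possible reverse causation to the limitations in section 5.1.

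The cost is wording and one regrouped results table, with no change to instruments, sample or models. The downside is that the conclusions become less strong. The article states that recruitment has not begun, so the changes can be made before any data exist.
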